### Randomization

A computer generated random allocation sequence will be applied to randomize the PHC centers to either intervention or control conditions with a 1:1 ratio. Cluster-randomization will be employed at the PHC center level, meaning that all individual study participants recruited from a particular PHC center will receive the same treatment. This will be done due to feasibility reasons and to avoid contamination of the trial conditions. The PHC centers will be paired based on their socioeconomic index and allocated to the treatment conditions from each pair after they have agreed to participate, approximately one month before the PHC provider training. Each set of participating PHC centers will be randomized separately. The randomizations will be conducted by a statistician.

The PHC providers and study participants will not be blinded. However, the study participants will not be informed about the difference between the trial conditions until after the study. This will be done in order to avoid attrition and preconceptions regarding the treatment effectiveness that could affect the study results (risk that study participants in the control group could perceive standard treatment as less effective compared to TCP).

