### Study Setting and Participants

Study participants will be recruited from participating PHC centers located in socioeconomically disadvantaged areas in Stockholm County, Sweden. Eligible PHC centers will be identified based on a socioeconomic index, which takes into account the income, educational level, ethnicity and health status of the population in a PHC center’s catchment area [26]. Daily tobacco users over 18 years of age with Swedish social security numbers and permanent residence permits, fluent in one of the two most common languages in the study setting, Swedish or Arabic, will be eligible for inclusion in the study. Daily tobacco use will be defined as daily use of cigarettes, snus (smokeless tobacco) or other tobacco products for at least the last year. Ongoing treatment for tobacco cessation and cognitive impairment affecting ability to participate in the study on a voluntary basis will be applied as exclusion criteria.

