### Sample Size

The required sample size was calculated based on the primary outcome, assuming a 7% rate of 7-day prevalence in abstinence from tobacco use at 6 months follow-up in the control group, significance level of 5% and 80% power to detect a 2.0 relative risk of successful quit attempts in the intervention group compared to the control group. The estimated prevalence of abstinence in the control group corresponds to the success rate of brief advice [33] which is the minimum intervention for the control group in this study. The estimated relative risk corresponds to the relative risk of abstinence from tobacco use for combined pharmacotherapy and counseling, as recommended for the intervention group in this study, compared to minimal intervention or usual care [34]. The unadjusted sample size was found to be 300 per arm. Assuming an intra-cluster coefficient (ICC) of 0.01 according to Adams et al [35] the sample size was adjusted for design effect using the formula: 1 + (m − 1) ρ, where m represents the mean number of participants in each cluster and ρ is the ICC. Having 7 clusters per arm and 43 participants per cluster, the adjusted sample size will be 426 per arm. Finally adjusted for an attrition/drop-out of 8%, the final sample size will be 464 per arm or 928 in total. The estimated attrition rate of 8% is based on reported attrition rates from two other tobacco cessation trials with similar study designs, both conducted in the Swedish health care setting [30,36]. A higher number of participating PHC centers could decrease the required number of study participants without compromising the power to detect a statistically significant difference in the outcomes between the groups at follow-up, wherefore the aim is to recruit a total of 20 PHC centers. A total sample size of 840 would then be needed.

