### Statistical Analysis

In order to describe the setting and the effectiveness of the randomization, descriptive statistics of the study population’s baseline characteristics at both individual and cluster level will be presented separately for the intervention and control arm, as proportions for categorical variables and as mean values with corresponding standard deviation (SD) for continuous variables.

The association between the treatment and the outcomes post-intervention will be analyzed using multiple regression models. A logistic regression model will be used for binary outcomes, including the primary outcome, 7-day abstinence. The result will be presented as an odds ratio (OR) and corresponding 95% confidence interval (CI). The association between the treatment and continuous/count outcomes, including the secondary outcomes, daily tobacco consumption, number of quit attempts and health-related quality of life, will be analyzed using multiple linear and Poisson regression models. All analyses will be conducted according to the intention to treat principle [37], meaning that the individual study participants will be analyzed according to how the PHC centers where they were recruited and treated were randomized, regardless of which intervention they received. Inference will be targeted at the individual level and hierarchical models will be used to handle potential clustering on the PHC center level. Model covariates will include age, sex, educational level, nicotine dependence, motivation and readiness to quit, previous quit attempts, previous use of pharmacotherapy, and diagnosis of chronic disease. For main analysis no missing data will be imputed. However, classical multiple imputation methods will be used for an additional sensitivity analysis if any of the included variables have more than 5% missing observations. The analyses will be conducted by the research team, including a statistician.

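### Centres are paired on a socioeconomic index and randomised in separate sets, but the named model covariates include neither, so precision is lost if either predicts abstinence

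*Protocol article*

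**What the plan says.** The Randomization section restricts allocation in two ways. Centres are matched on the index: "The PHC centers will be paired based on their socioeconomic index and allocated to the treatment conditions from each pair". And: "Each set of participating PHC centers will be randomized separately". The Results section describes a first set of eight centres and a second set expected to start in September 2016.

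The index is a property of the centre. According to Study Setting and Participants it "takes into account the income, educational level, ethnicity and health status of the population in a PHC center’s catchment area".

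The Statistical Analysis section says that "hierarchical models will be used to handle potential clustering on the PHC center level" and then lists the adjustment variables: "Model covariates will include age, sex, educational level, nicotine dependence, motivation and readiness to quit, previous quit attempts, previous use of pharmacotherapy". One further item closes the list, a chronic-disease diagnosis. Counting motivation and readiness as one item, that is eight variables, all measured on the participant. Cluster-level characteristics appear in that section only as descriptive statistics by arm.

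**The concern.** Pairing makes the arms alike on the index, so the true sampling variance of the treatment contrast falls by whatever the index explains. A model that leaves the index out does not see that reduction. The explained part stays in the centre-level variance, and the standard error is computed as if centres had been allocated freely. The same holds for the set, which the separate randomisations balance across arms.

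What is at stake is precision. With only 14 to 20 centres, between-centre variance is a large part of the uncertainty. The protocol names its covariates down to previous drug treatment, yet not the variable by which it constrains allocation. Adding that variable once outcomes are known would be a post hoc choice.

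**Working it through.** **1. The plan's own figure.** Inputs from the Sample Size section: 7% against 14% (relative risk 2.0), 5% significance (two-sided reproduces), 80% power, ICC 0.01, 7 clusters per arm, 43 per cluster, 8% dropout.
- Two proportions, pooled variance, no continuity correction: 300 per arm.
- Design effect 1 + (43 − 1) × 0.01 = 1.42, and 300 × 1.42 = 426.
- 426 / 0.92 = 463.04, rounded up to 464 per arm, or 928 in total.

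The figure reproduces. The design effect is the unmatched one, so no gain from pairing is built in.

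**2. Precision with and without the index.** Let J be centres per arm, m analysed participants per centre, ρ = 0.01, and R² the share of between-centre variance explained by the index and set beyond the listed covariates. The documents give no R², so 0 to 50% is an assumption.

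SE² = [0.07 × 0.93 + 0.14 × 0.86] / (J·m) × [(1 − ρ) + m·ρ·(1 − R²)]

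The first bracket is 0.0651 + 0.1204 = 0.1855. Power is from the non-central t distribution with non-centrality 0.07/SE. Degrees of freedom are 2J − 2 for the planned model, 2J − 4 with index and set added, and J − 1 with one indicator per pair.

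*7 centres per arm.* 464 × 0.92 ≈ 427 analysed per arm, so m = 61. Planned model: multiplier 0.99 + 0.61 = 1.60, SE = √(0.1855/427 × 1.60) = 0.0264, power 68.4%.

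*10 centres per arm, 840 in total.* 300 × 1.29 = 387 analysed per arm, so m = 38.7. Planned model: multiplier 0.99 + 0.387 = 1.377, SE = 0.0257, power 73.1%.

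| R² (assumed) | 7 per arm: SE | index + set | pair indicators | 10 per arm: SE | index + set | pair indicators |
|---|---|---|---|---|---|---|
| 0% | 0.0264 | 66.8% | 60.3% | 0.0257 | 72.5% | 68.0% |
| 20% | 0.0253 | 70.2% | 63.7% | 0.0250 | 75.0% | 70.5% |
| 30% | 0.0248 | 72.0% | 65.5% | 0.0246 | 76.2% | 71.8% |
| 50% | 0.0237 | 75.8% | 69.3% | 0.0238 | 78.8% | 74.4% |

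On the risk-difference scale, as a guide to the odds ratio, the interval with 7 centres per arm changes in width by the SE ratio times the ratio of t quantiles. At R² = 50% this is 0.900 × 2.228/2.179 = 0.92, or 8% narrower. At R² = 0 it is 1.000 × 2.228/2.179 = 1.02, or 2% wider.

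The starting levels lie below 80% because the centres hold 61 or about 39 analysed participants, not the 43 or 30 used in the design effect, and because t quantiles are used. That is a separate matter. Only the differences belong to this point.

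**3. Direction of the error.** A simulation with 7 pairs of 61, ICC 0.01 and 8,000 runs per cell (index only, set not simulated) gave these results:

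| R² | Type I error, index ignored | Power, ignored | Power, index in model |
|---|---|---|---|
| 0% | 5.1% | 74% | 72% |
| 50% | 3.0% | 74% | 79% |
| 90% | 2.0% | 76% | 85% |

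The power levels are higher than in the formula, so compare within this table only. The pattern agrees: without the index the test falls below its nominal 5% and gains almost nothing from the pairing. With the index in the model, type I error stayed at 4.9% to 5.1%.

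**The case against.** The strongest reply is that nothing is broken. The analysis is valid, the sample size does not rely on pairing, and a conservative test is the safer error. All of that stands. A reader might infer bias or an inflated type I error from the omission; the calculations show the opposite direction.

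The gain is also conditional. Nothing in the protocol says how far the index predicts quitting between centres. Eligible centres all lie in disadvantaged areas, which narrows the range of the index and may weaken it as a predictor. Two of its four domains also have participant-level counterparts in the model: educational level, and chronic disease for health status. These are reasons to include zero in the range. They do not put the index in the model, and income and ethnicity have no counterpart on the list.

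A reader might also infer that start-up differences between the two sets distort the comparison. They do not, because separate 1:1 randomisation of each set balances it across arms. The set matters only for precision, and no figure for its variance is available.

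Finally, the covariate sentence leaves room for additions, and an analysis plan that is not shown may contain them. That is fair, but the list given here is specific and commits to neither variable.

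**Conclusion.** The point holds as a conditional loss of efficiency: the stated model does not reflect the stated restriction of the randomisation. Across an assumed 0 to 50% of between-centre variance explained, adding the index and set changes power by about −2 to +7 points with 7 centres per arm, and by about −1 to +6 points with 10 per arm and 840 participants. This rests on the protocol's ICC of 0.01, rates of 7% and 14%, 8% dropout, equal cluster sizes and a centre-level t approximation.

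It is tempting to conclude that using the pairing factor would bring 14 centres to 80% power. It does not in this range: 30% explained gives about 72%, and 50% about 76%. Nor does the omission make the stated 928 wrong.

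**What to change.** Add one sentence to the Statistical Analysis section: every outcome model will include the centre's socioeconomic index (continuous) and the randomisation set (first or second) as centre-level fixed effects, alongside the listed covariates. Fix this before outcomes are seen.

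Do not use 7 to 10 pair indicators. They leave 6 to 9 between-centre degrees of freedom instead of 10 to 16, and in the table they have lower power than index plus set in every row.

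No new data are needed, since the index was used to select and pair the centres. The cost is two between-centre degrees of freedom: if neither variable is prognostic, power falls from 68.4% to 66.8% with 7 centres per arm and from 73.1% to 72.5% with 10.

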### Statistical Analysis

In order to describe the setting and the effectiveness of the randomization, descriptive statistics of the study population’s baseline characteristics at both individual and cluster level will be presented separately for the intervention and control arm, as proportions for categorical variables and as mean values with corresponding standard deviation (SD) for continuous variables.

The association between the treatment and the outcomes post-intervention will be analyzed using multiple regression models. A logistic regression model will be used for binary outcomes, including the primary outcome, 7-day abstinence. The result will be presented as an odds ratio (OR) and corresponding 95% confidence interval (CI). The association between the treatment and continuous/count outcomes, including the secondary outcomes, daily tobacco consumption, number of quit attempts and health-related quality of life, will be analyzed using multiple linear and Poisson regression models. All analyses will be conducted according to the intention to treat principle [37], meaning that the individual study participants will be analyzed according to how the PHC centers where they were recruited and treated were randomized, regardless of which intervention they received. Inference will be targeted at the individual level and hierarchical models will be used to handle potential clustering on the PHC center level. Model covariates will include age, sex, educational level, nicotine dependence, motivation and readiness to quit, previous quit attempts, previous use of pharmacotherapy, and diagnosis of chronic disease. For main analysis no missing data will be imputed. However, classical multiple imputation methods will be used for an additional sensitivity analysis if any of the included variables have more than 5% missing observations. The analyses will be conducted by the research team, including a statistician.

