### Data Collection

Data on sociodemographic characteristics, tobacco use, and nicotine dependence, previous quit attempts, self-efficacy and motivation to quit, health status and health-related quality of life will be collected through patient questionnaires. The questionnaires are based on questions from the Swedish Public Health Survey 2014 [29], a questionnaire that was used in a previous study that evaluated the effectiveness of brief advice for tobacco cessation in dental practices in Sweden [30] and the Swedish and Arabic (Lebanon) version of the EQ-5D-5L instrument [31]. Questions not included in the EQ-5D-5L questionnaire were translated from Swedish to Arabic and back by two different professional translation agencies and critically reviewed by a research assistant fluent in both Swedish and Arabic. The questionnaires were pilot tested in Swedish prior to the study start and in Arabic prior to the recruitment of Arabic speaking participants.

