The measurements will be conducted at baseline (before the intervention) and 6 and 12 months after the intervention. In the follow-up questionnaires, questions regarding the tobacco cessation-related care the patients have received during the study period have been added. The baseline questionnaires will be administered by staff responsible for the treatment of patients at the participating PHC centers. The PHC providers administering the treatment will also document what treatment the patients have received (duration, content, intensity and number of visits, mode of counseling, referrals, any recommended and prescribed pharmacotherapy, follow-ups, etc) in the electronic medical records and in study specific documentation protocols. Staff will be educated in the documentation procedures before the start of the study. The follow-up questionnaires will be sent to the participants via mail by the researchers to avoid attrition caused by additional costs and administrative burden of revisits for the study participants. A reminder with a new follow-up questionnaire attached will be sent out via mail by the researchers if the follow-up questionnaire is not returned within ten days. If the reminder questionnaire is not returned, additional reminders to return the questionnaire will be sent out via mail, email and SMS text messaging (short message service, SMS) by the researchers. In connection with the second reminder, the participants will be offered the opportunity to answer the questionnaire in a telephone interview. Multiple reminders and forms of contact have been found essential in promoting high retention rates among disadvantaged research participants who are often highly mobile [32]. The strategy above is expected to be sufficient in reaching study participants who are willing to respond to the follow-up questionnaires. Arabic speaking staff will assist the researchers in contacting and collecting data from the Arabic speaking participants.

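### The covariate list for the secondary-outcome models omits baseline EQ-5D and baseline daily consumption, so two secondary effects are less precise than they could be and partly exposed to baseline imbalance

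*Protocol article*

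**What the plan says.** All quotes are from the protocol article.

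- **What is modelled** (Statistical Analysis): "The association between the treatment and the outcomes post-intervention will be analyzed using multiple regression models". The target is the follow-up value; no change from baseline is mentioned.
- **Which secondary outcomes** (Statistical Analysis): "daily tobacco consumption, number of quit attempts and health-related quality of life, will be analyzed using multiple linear and Poisson regression models".
- **Covariates** (Statistical Analysis): "Model covariates will include age, sex, educational level, nicotine dependence, motivation and readiness to quit, previous quit attempts, previous use of pharmacotherapy" and, closing the list, "and diagnosis of chronic disease". No addition is named for any particular outcome.
- **What is collected** (Data Collection): "tobacco use, and nicotine dependence, previous quit attempts, self-efficacy and motivation to quit, health status and health-related quality of life will be collected" by patient questionnaire. The quality-of-life measure is "the Swedish and Arabic (Lebanon) version of the EQ-5D-5L instrument".
- **When** (Data Collection): "The measurements will be conducted at baseline (before the intervention) and 6 and 12 months after the intervention".

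**The concern.** For an outcome measured on the same scale before and after treatment, the baseline value is usually the best single predictor of the follow-up value. Here it is collected for quality of life and, on a natural reading of the tobacco-use questions, for daily consumption. It enters neither model. The third of these secondary outcomes, quit attempts, does have a baseline counterpart on the list (previous quit attempts), so the treatment of the three is uneven.

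Two things are at stake. The first is precision, because explainable variation stays in the residual. The second is exposure to baseline differences between arms. Only 14-20 centres are randomised, and they are paired on a socioeconomic index alone. The first eight were allocated in 2015, and individual recruitment was still under way after provider training in February and April 2016. Recruiters are appointed staff of those centres, and providers are not blinded. Baseline differences can therefore arise by chance or through selective recruitment.

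**Working it through.** **1. The plan's own figure.** The Sample Size section assumes 7% against 14% (relative risk 2.0), a 5% level (taken as two-sided) and 80% power. With the pooled variance under the null:

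n = [1.960·√(2·0.105·0.895) + 0.8416·√(0.07·0.93 + 0.14·0.86)]² / 0.07² = (0.8497 + 0.3625)² / 0.0049 ≈ 300 per arm.

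Design effect 1 + (43 − 1)·0.01 = 1.42; 300·1.42 = 426; 426/0.92 ≈ 464 per arm; 928 in total. This reproduces the stated figures. They rest on the binary primary outcome, and the protocol gives no calculation for the secondary outcomes.

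**2. Starting precision for a continuous secondary outcome.** Inputs: 426 evaluable per arm, 7 centres per arm, ICC 0.01. That ICC was set for abstinence; its use here is an assumption. The cluster size is 426/7 ≈ 60.9.

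- Variance multiplier = individual part 0.99 + centre part 60.9·0.01 ≈ 0.609, total ≈ 1.599.
- Effective n = 426/1.599 ≈ 266 per arm.
- SE = √(2/266) ≈ 0.087 SD.
- Detectable difference at 80% power = 2.80·0.087 ≈ 0.243 SD.

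SD here means the residual SD after the listed covariates.

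**3. Adding the baseline value.** Let r be the partial correlation of baseline with follow-up, given the covariates already listed. The documents give no value, so 0.2-0.7 is assumed.

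- *Case A:* individual and centre variance shrink equally. SE factor = √(1 − r²).
- *Case B:* only individual variance shrinks. SE factor = √{[0.99(1 − r²) + 0.609]/1.599}.
- *Carry-over:* without the baseline term, an imbalance of 0.2 SD (the part the listed covariates do not explain) moves the estimate by about 0.2·r, taking equal SDs at baseline and follow-up.

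| r | 1 − r² | SE falls, case A | Multiplier, case B | SE falls, case B | Carry-over of 0.2 SD |
|---|---|---|---|---|---|
| 0.2 | 0.96 | 2% | 1.559 | 1% | 0.04 SD |
| 0.3 | 0.91 | 5% | 1.510 | 3% | 0.06 SD |
| 0.5 | 0.75 | 13% | 1.351 | 8% | 0.10 SD |
| 0.7 | 0.51 | 29% | 1.114 | 17% | 0.14 SD |

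Under case A the detectable difference falls from 0.243 SD to 0.238, 0.232, 0.210 and 0.173 SD respectively.

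**4. Is an imbalance of that order plausible?** The SD of a chance baseline difference between arms is √(2·DE/426), ignoring any gain from pairing. At ICC 0.01, DE = 1.599 and the SD is about 0.09. At an assumed ICC of 0.05, DE = 1 + 59.9·0.05 ≈ 3.99 and the SD is about 0.14. A difference of 0.1-0.2 SD can thus occur by chance. A carry-over of 0.04-0.14 SD equals roughly 0.5 to 1.6 of the 0.087 SD standard error.

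**The case against.** **The list may not be closed.** The article says what the covariates will include, not that nothing else will be added, and outcome-specific terms could stand in an analysis plan that is not shown. This limits the point: it is not a contradiction in the protocol. It does not remove it, because a specific list is printed, no baseline value of these outcomes is on it, and following it as written gives the weaker analysis.

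**The listed covariates are partial proxies.** Nicotine dependence overlaps with baseline consumption, and chronic disease with baseline quality of life. This stands, and it is why r must be a partial correlation. For consumption, where quitters drop to zero, r probably lies toward the lower end.

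**A larger gain is tempting but unsupported.** A reader might take a correlation of 0.5-0.7 and infer a standard error 13-29% smaller, or the equivalent of 1.3-2.0 times the participants. That treats the correlation as if nothing else were adjusted for. It also assumes that centre-level variance shrinks as much as individual variance; if it does not, the same correlations give 8-17%. Nor would more participants in a fixed number of centres buy precision at that rate. The 1 − r² rule is in any case a linear-model result, and the protocol does not say whether consumption gets a linear or a Poisson model.

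**Imbalance does not transfer in full.** A reader might infer that any baseline difference passes whole into the effect. It carries over only in proportion to the partial slope. There are also safeguards: the pairing index takes in the health status of the catchment population, and candidates are identified by a screening questionnaire before invitation. These reduce imbalance without excluding it.

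**Conclusion.** The point holds for two secondary outcomes, quality of life and daily consumption. The omission and the direction of its effect are well supported; its size is not known. Over the assumed partial correlations of 0.2-0.7, the avoidable excess in standard error ranges from negligible (1-2%) to material (17% or 29%, depending on whether centre-level variance also shrinks). The exposure to a 0.2 SD imbalance is about 0.04-0.14 SD.

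A reader might extend this to the main result, which the documents do not support. Every participant is a daily user at entry, so 7-day abstinence has no baseline value to adjust for, and the sample size of 928 is untouched. Nor does the Economic Evaluation section say that the between-arm EQ-5D estimate drives the cost-effectiveness model.

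One link is inferred: that the baseline tobacco-use questions record daily consumption in the unit of the outcome. The article does not say so outright.

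**What to change.** Add one sentence to Statistical Analysis: the quality-of-life model also includes the baseline EQ-5D index, and the consumption model also includes baseline daily consumption in the same unit as the outcome. Keep the rest of the list.

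The cost is that sentence, settled before outcome data are analysed. No new data are needed, provided the baseline questionnaire records daily consumption as expected. Because the main analysis imputes nothing, anyone without the baseline value would drop out of that one model; the multiple-imputation sensitivity analysis already planned would cover this if more than 5% are missing. The primary analysis and the sample size do not change.

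### The main analysis keeps complete cases only, so more than the planned 8% may be lost, and no named analysis tests arm-differential non-response to the abstinence questionnaire

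*Protocol article*

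**What the plan says.** Under Statistical Analysis, the primary outcome is analysed by logistic regression, and "hierarchical models will be used to handle potential clustering on the PHC center level". The adjustment set is fixed: "Model covariates will include age, sex, educational level, nicotine dependence, motivation and readiness to quit, previous quit attempts, previous use of pharmacotherapy, and diagnosis" (this last item refers to chronic disease). That is eight items, or nine if motivation and readiness are separate variables.

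On missing data the section gives one rule and one fallback. The rule is "For main analysis no missing data will be imputed". The fallback is that "classical multiple imputation methods will be used for an additional sensitivity analysis if any of the included variables have more than 5% missing observations". The section also says "All analyses will be conducted according to the intention to treat principle", which it defines as analysis by the allocation of the recruiting centre.

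Under Sample Size, the only allowance for loss is this: "Finally adjusted for an attrition/drop-out of 8%, the final sample size will be 464 per arm or 928 in total".

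Under Data Collection, clinic staff administer the baseline questionnaire. Follow-up is by mailed questionnaire with reminders and a telephone option.

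**The concern.** A regression fitted without imputation uses only participants with the outcome and every covariate. A participant whose 6-month abstinence is known is discarded for one blank baseline item. The sample size has no margin for that, because its 8% is described as attrition or drop-out.

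The second issue is who fails to reply. Abstinence is self-reported, mostly by post, in an unblinded trial. Continuing users may be less willing to reply than abstainers, and the size of that gap may differ by arm. If so, the odds ratio among responders is biased. Multiple imputation as ordinarily done fills in non-responders from participants who look alike on observed data, so it would not show the problem. Nothing else named in the article would either.

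**Working it through.** **1. The plan's own figure.** Inputs from Sample Size: 7% versus 14% (relative risk 2.0), 5% significance (taken as two-sided), 80% power, intra-cluster coefficient 0.01, cluster size 43, attrition 8%.
- The pooled-variance two-proportion formula gives 300 per arm.
- Design effect: 1 + (43 − 1) × 0.01 = 1.42, and 300 × 1.42 = 426.
- 426 / 0.92 = 463.04, rounded up to 464 per arm, or 928 in total. The stated chain reproduces.

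**2. Loss from blank covariates.** Let q be the share blank on each of eight covariates, independently. This is an assumption, as the article gives no rate. The share kept is 0.92 × (1 − q)^8. For q = 2%: 0.92 × 0.98^8 = 0.783, which is 363 of 464.

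Power uses the cluster size that the analysed number implies: m = n/k with k centres per arm, design effect 1 + (m − 1) × 0.01, and n_eff = n / design effect. Then power = Φ[(0.07 − 1.96·√(2 × 0.105 × 0.895 / n_eff)) / √((0.07 × 0.93 + 0.14 × 0.86) / n_eff)].

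| q | total loss | n per arm | power, 14 centres | power, 20 centres |
|---|---|---|---|---|
| 0 | 8.0% | 427 | 75.2% | 80.2% |
| 0.5% | 11.6% | 410 | 74.2% | 79.1% |
| 1% | 15.1% | 394 | 73.1% | 77.9% |
| 2% | 21.7% | 363 | 70.8% | 75.5% |
| 3% | 27.9% | 335 | 68.5% | 72.9% |

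Both power columns hold the total at 928. The article would need only 840 with 20 centres.

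The 14-centre column starts at 75%, not 80%, for a separate reason. About 427 per arm over 7 centres is 61 per centre, not 43, so the design effect is 1.60. Only the fall within a column, about 1 to 7 points, belongs to this point.

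**3. The imputation trigger.** The planned 8% loss already exceeds 5% for the outcome, so the multiple imputation would be expected to run. The threshold itself is not the problem.

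**4. Differential non-response.** Let a be the response rate in abstainers and u the rate in continuing users. The observed abstinence rate is p·a / [p·a + (1 − p)·u], so the observed odds are the true odds times a/u. The odds ratio is therefore multiplied by (a/u in intervention) / (a/u in control).
- Assume a = 0.95 in both arms, with u = 0.90 in control and 0.80 in intervention. The factor is 0.90/0.80 = 1.125.
- The design odds ratio is (0.14/0.86) / (0.07/0.93) = 2.16, which reads 2.163 × 1.125 = 2.43. A null reads 1.125.
- If a and u are the same in both arms, the factor is 1 and the odds ratio is unbiased, although the abstinence rates themselves are not.
- With the arms reversed, the factor is 0.80/0.90 = 0.889 and 2.16 reads 1.92. The direction is not known in advance.

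**5. Counting non-responders as users.** In that scenario the rates are 0.07 × 0.95 = 0.0665 and 0.14 × 0.95 = 0.133, so the relative risk is 2.0. If abstainers respond at 95% in control but 85% in intervention, it becomes (0.14 × 0.85) / (0.07 × 0.95) = 1.79, and a null becomes 0.89.

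**The case against.** Several stronger readings are tempting, and the article does not support them.

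- *The rule contradicts intention to treat.* A reader might infer this. The article defines the principle as analysis by centre allocation, and leaving out incomplete records does not breach that definition.
- *More than 8% will be lost.* This depends on covariate missingness that the article does not report. Staff administer the baseline questionnaire, age and sex should rarely be blank, and blanks tend to fall in the same people, so eight independent blanks is a pessimistic model. With complete covariates the loss is 8%.
- *The imputation is single-level and assumes missing at random.* Neither is written. The article says only that the methods are classical, and an analysis plan not shown may specify the model.
- *Power falls from 80% to about 70% because of this rule.* With 14 centres, about 5 of those points come from the cluster-size issue in step 2 of the working.

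Mitigation is also real: reminders by mail, email and SMS, a telephone interview, a gift certificate, and not telling participants how the arms differ until after the study. These measures should reduce non-response, but they do not test its effect.

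What remains is that the article itself states the main rule and its only fallback. This is therefore a choice open to criticism, not detail left for later.

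**Conclusion.** The point holds as a weakness in a stated rule. The main analysis excludes anyone missing the 6-month outcome or a listed covariate, while the 8% allowance covers attrition only. If each of eight covariates is independently 0.5-3% blank, total loss is 12-28% and power at 928 drops by about 1 to 7 points from its complete-covariate value. With complete covariates this cost disappears.

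Separately, no named analysis would reveal response that depends on tobacco use and differs by arm. Under the assumed response rates the odds ratio is distorted by a factor of 1.125. The bias needs both conditions, and its size rests wholly on those rates. The figure of 928 is not shown to be wrong by this point.

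**What to change.** 1. In the main analysis, keep everyone with a 6-month outcome and fill missing baseline covariates without reference to the outcome (mean or missing-indicator). Report covariate missingness by arm: unblinded staff collect baseline data after centres are allocated, so it may itself differ by arm.
2. Pre-specify, as a sensitivity analysis only, the primary outcome with non-responders counted as tobacco users in both arms, ideally with departures that vary by arm. It cannot replace the main analysis, because it is biased if abstainers' response differs by arm (step 5 of the working).
3. State that the multiple imputation model includes centre and arm. Arm is constant within a centre, so centre is best entered as a random effect. Dropping the 5% trigger would change little, since the planned attrition already meets it.

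The cost is analysis wording and two extra model runs. There is no change to design, recruitment or participant burden.
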